## 11.2 Sample Size

The primary objective of this study is to evaluate the efficacy and safety of TQB2858 injection in advanced high-grade sarcoma, and it is planned to include 30 ~ 100 subjects (Cohort 1:10 ~ 30 subjects with primary alveolar soft part sarcoma; Cohort 2:10 ~ 30 subjects with alveolar soft part sarcoma failing to receive PD-1 therapy; Cohort 3:10 ~ 40 subjects with other subtypes (pleomorphic sarcoma, classical osteosarcoma, Ewing sarcoma, chondrosarcoma and dedifferentiated liposarcoma, etc.)). The final sample size is adjusted according to the specific situation of the trial.

## 11.3 Statistical Analysis

### 11.3.1 General Principles

PK parameter calculations will be performed using Phoenix WinNonlin 7.0 or later version, and all other statistical analyses will be programmed and calculated using SAS 9.4 or later version of Statistical Analysis Software. Number of cases and missing cases for summary analysis. Quantitative data are generally described by mean, standard deviation, median, quartiles, minimum and maximum. For some quantitative data, additional statistics such as geometric mean and coefficient of variation are analyzed.

Qualitative and hierarchical data are generally described by frequency and percentage. Statistical test showed that the test level was  $\alpha = 0.05$ , P value  $\leq 0.05$ , which was judged as statistically significant.

### **11.3.2 Hypothesis Testing**

None

### **11.3.3 Subject Disposition**

The exact number of all subjects who entered the study from the screening period to the completion of the study and the number of subjects who were enrolled and included in each analysis set, and the number of subjects who completed the trial and withdrew from the trial was described. Subjects who fail screening will be grouped and summarized by primary reason, and subjects who prematurely discontinue treatment after enrollment will be grouped and summarized by dose group and primary reason.

Subject disposition in each data set: subject disposition in each analysis population was summarized, and the reasons for excluding subjects in each analysis population were summarized. Subjects excluded from each analysis population were tabulated by treatment group (including protocol deviations and reasons for exclusion).

### **11.3.4 Demographic and Baseline Characteristics**

Baseline characteristics were defined as nonmissing assessments before first drug intake.

The demographic characteristics and baseline characteristics of all subjects will be statistically described. For quantitative data, describe the mean, standard deviation, median, quartile, maximum and minimum; for qualitative data, list the frequency and percentage.

### **11.3.5 Safety Analysis**

- 1) Summarize the exposure of subjects to the study drug, including the number of cycles completed, dose modifications during treatment, and the cumulative number of dose modifications during treatment.

The treatment time, total dose and average daily dose of the investigational drug

during the treatment period will be statistically described.

## 2) Adverse events

All adverse events (AEs) will be classified according to the current version of the Medical Dictionary for Regulatory Activities (MedDRA) at the time of coding and graded according to CTCAE v5.0.

### Treatment Emergent Adverse Events (TEAE)

A TEAE was defined as an adverse event that appeared after or worsened after study drug administration.

a) The following adverse events were summarized by actual treatment:

- All adverse events (AEs);
- Treatment-emergent adverse events (TEAEs);
- TEAE judged to be DLT
- Grade 3 and above TEAEs;
- Serious adverse events (SAEs);
- TEAE leading to dose interruption and termination;
- TEAEs related to the study drug;
- Grade 3 and above TEAEs related to the study drug;
- SAEs related to the study drug;
- TEAEs related to the study drug leading to dose interruption and termination;

b) Describe the number and incidence of adverse events listed above by dose group, sorted by system organ class SOC and preferred term PT.

c) Number of cases and incidence of each toxicity grade of NCI CTCAE version 5.0 will be calculated according to actual treatment group, SOC and PT classification, respectively (for repeated occurrence of the same AE, the number of cases with the highest grade and the toxicity grade of the incidence will be analyzed).

d) Analysis of time to first TEAE

Time to first TEAE = date of first TEAE – date of first dose + 1. The analysis will be performed at overall level and at SOC and PT level. Only TEAEs judged as DLT will

be analyzed.

Provide detailed list of subjects with adverse events and detailed list of subjects with SAE.

### 3) Laboratory tests

For continuous variables, number of cases, mean, standard deviation, median, quartiles, minimum and maximum will be described at baseline and each visit by dose group, and mean, standard deviation and 95% CI will be described for changes from baseline.

### 4) 12-Electrocardiogram

For ECG continuous variables, number, mean, standard deviation, median, quartiles, minimum and maximum will be described at baseline and each visit by dose group, and mean, standard deviation and 95% CI will be described for changes from baseline.

The ECG examination results at each visit will be descriptively summarized for each dose group, and classified into normal, abnormal without clinical significance and abnormal with clinical significance. Cross-classification table will be used to compare with baseline ECG results.

### 5) Vital Signs and Weight

The results of vital signs and body weight will be summarized descriptively by visit for each dose group, including the mean, standard deviation, median, quartiles, minimum and maximum of observed values at each time point, and the mean, standard deviation and 95% CI will be described for the changes from baseline.

### 6) ECOG score

Results of ECOG scores at baseline and at each visit were summarized descriptively by dose, by score, and descriptively by frequency and percentage using cross-classification tables.

## 11.3.6 Concomitant Medication

Summarize the use of concomitant medications during the trial (including any

changes in concomitant medications during the screening period, new concomitant medications after screening and concomitant medications during the follow-up period) and the frequency of use of each drug. WHODrug Global will be used for coding, and frequency summary description will be performed based on SS population by anatomic classification (ATC first layer coding) and therapeutics (ATC second layer coding).

### **11.3.7 Evaluation of Anti-tumor Clinical Efficacy**

The anti-tumor efficacy of TQB2858 injection will be preliminarily evaluated in this trial. Efficacy analyses were based on the Efficacy Assessment Analysis Set (EAS). Efficacy evaluation indicators mainly include: objective response rate (ORR), disease control rate (DCR), progression-free survival (PFS), overall survival (OS) and duration of response (DOR), 3-month ORR, etc.

Objective response rate (ORR): The proportion of objective response cases (PR + CR) in the total number of cases and its 95% CI will be calculated. The 95% CI for ORR was calculated based on the exact binomial method using the F-distribution.

Disease control rate (DCR): The proportion of disease control cases (PR + CR + SD) in total cases and its 95% CI will be calculated. The 95% CI for DCR was calculated based on the exact binomial method of the F-distribution.

Progression-free survival (PFS): PFS and its 95% CI were estimated using the Kaplan-Meier method, and Kaplan-Meier curves were plotted.

Overall survival (OS): OS and its 95% CI will be estimated using the Kaplan-Meier method and the Kaplan-Meier curve will be plotted.

Duration of response (DOR): Kaplan-Meier method was used to estimate DOR and its 95% CI, and Kaplan-Meier curve was plotted. Only analyzed for responders.

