Pembrolizumab, in clinical studies with SARC028, included STS patients over 18 years of age or osteosarcoma patients over 12 years of age with histological evidence of metastatic or surgically unresectable locally advanced sarcoma that could have received up to 3 prior lines of therapy. Pembrolizumab 200 mg intravenously every 3 weeks for the primary endpoint of objective response rate (ORR). Of the 80 evaluable patients, only 7 (18%) of 40 STS patients had an objective response to pembrolizumab treatment, including 4 (40%) of 10 undifferentiated pleomorphic sarcomas, 2 (20%) of 10 liposarcomas, 1 (10%) of 10 synovial sarcomas, and none of 10 leiomyosarcomas. Among 40 cases of osteosarcoma, only 2 cases (5%) had objective response, including 22 cases of osteosarcoma in 1 case (5%), 5 cases of chondrosarcoma in 1 case (20%), and 13 cases of Yuvonn's sarcoma did not respond to treatment. Soft tissue sarcoma cohort, ORR 18%, mDOR 33 weeks, mPFS 18 weeks, PFS rate 55% at 12 weeks, mOS 49 weeks; undifferentiated pleomorphic sarcoma mPFS 30 weeks, PFS rate 70% at 12 weeks; liposarcoma mPFS 25 weeks, PFS rate 60% at 12 weeks.

Sarcoma subtypes are numerous, with high recurrence rate and poor prognosis. With the gradual deepening of the understanding of sarcoma tissue and biological behavior, immunotherapy will become a new therapeutic hope for sarcoma in the future.

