### **2.4 Primary Endpoints**

- ORR based on RECIST 1.1 and iRECIST;

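### Section 11 states the primary ORR only over all cases, although three unlike cohorts of open size are enrolled, and its safety tables use dose groups and DLTs that this one-dose-level trial does not define

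*Protocol*

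**What the plan says.** **Design.** Protocol sections 3, 4.1 and 11.2 describe three cohorts:

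- Cohort 1: primary alveolar soft part sarcoma (ASPS), 10-30 patients.
- Cohort 2: ASPS after failure of PD-1 therapy, 10-30 patients.
- Cohort 3: other subtypes, including pleomorphic sarcoma, osteosarcoma, Ewing sarcoma, chondrosarcoma and dedifferentiated liposarcoma, 10-40 patients.

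The total is 30-100. Section 11.2 closes with "The final sample size is adjusted according to the specific situation of the trial".

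**Efficacy.** Section 2.4 gives the primary endpoint as "ORR based on RECIST 1.1 and iRECIST", with no cohort named. Section 11.3.7 bases efficacy on one undivided analysis set (EAS) and says "The proportion of objective response cases (PR + CR) in the total number of cases and its 95% CI will be calculated", adding that "The 95% CI for ORR was calculated based on the exact binomial method using the F-distribution". DCR is also one proportion of all cases, and PFS, OS and DOR each get one Kaplan-Meier estimate. The synopsis uses the same denominator for ORR and DCR. Within section 11, cohorts are mentioned only under Sample Size. Section 11.3.2 states that there is no hypothesis test.

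**Safety and disposition.** Section 5.4.1 gives one dose level, the RP2D from phase 1, and section 5.4.2 allows no dose adjustment. Yet early discontinuations are "grouped and summarized by dose group and primary reason" (11.3.3), and for adverse events the plan is to "Describe the number and incidence of adverse events listed above by dose group" (11.3.5). Laboratory tests, ECG, vital signs, weight and ECOG are also split by dose group or dose. Section 11.3.5 lists a summary of TEAEs judged to be DLTs, and it limits the time-to-first-TEAE analysis: "Only TEAEs judged as DLT will" be analysed.

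**The concern.** A reader would expect a trial built on three cohorts to report its primary endpoint for each of them. One cohort is defined by failure of treatment on the PD-1/PD-L1 axis, which the study drug also targets. Another mixes histologies for which the protocol's own background reports very different response rates. A single proportion over all three is a weighted average whose weights are the enrolled cohort sizes, and those sizes may vary widely. Two conducts of this trial with the same drug effect in every cohort could then report different headline ORRs.

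The safety text raises a different problem. It uses a stratifier with only one level, and it restricts one analysis to events for which the protocol gives no definition, window or assessment. The abbreviation DLT occurs only in the abbreviation list and in section 11.3.5. The spelled-out term appears once more, in section 1.2.3, about other drugs.

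**Working it through.** **1. The protocol's own figure.** The total is the sum of the cohort ranges: 10 + 10 + 10 = 30 and 30 + 30 + 40 = 100. This reproduces 30-100. There is no power or precision figure to reproduce, because no null rate, target rate or interval width is stated.

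**2. How far the weights can move.** The share of cohort *k* is n_k / (n_1 + n_2 + n_3).

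- Cohort 1: from 10/80 = 12.5% to 30/50 = 60%.
- Cohort 2: the same, 12.5% to 60%.
- Cohort 3: from 10/70 = 14.3% to 40/60 = 66.7%.

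**3. Effect on the overall ORR.** The expected overall ORR is (n_1 p_1 + n_2 p_2 + n_3 p_3) / (n_1 + n_2 + n_3). Its extremes lie at corners of the permitted size ranges. The protocol gives no ASPS rate, so p_1 and p_2 are assumptions. For p_3 I take 9/80 = 11.25%, the combined response in the pembrolizumab sarcoma trial cited in section 1.1 (7 of 40 soft tissue plus 2 of 40 bone sarcomas). That is another drug, and its population includes synovial sarcoma and leiomyosarcoma, which Cohort 3 does not name.

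| Assumed p_1 / p_2 / p_3 | Lowest (sizes) | Highest (sizes) |
|---|---|---|
| 40% / 10% / 11.25% | (4 + 3 + 4.5)/80 = 14.4% (10/30/40) | (12 + 1 + 1.125)/50 = 28.3% (30/10/10) |
| 20% / 15% / 11.25% | (2 + 1.5 + 4.5)/60 = 13.3% (10/10/40) | (6 + 1.5 + 1.125)/50 = 17.3% (30/10/10) |
| all equal | no change | no change |

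**4. What one interval can hide.** Take a hypothetical full-size trial with 12/30, 3/30 and 4/40 responders. Exact (Clopper-Pearson) 95% intervals are:

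- Overall: 19/100 = 19% (11.8-28.1%).
- Cohort 1: 40% (22.7-59.4%).
- Cohort 2: 10% (2.1-26.5%).
- Cohort 3: 10% (2.8-23.7%).

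The overall interval excludes the Cohort 1 point estimate and does not show that the other two cohorts respond at 10%.

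**5. Heterogeneity inside Cohort 3.** Section 1.1 cites "including 4 (40%) of 10 undifferentiated pleomorphic sarcomas", against 1 of 22 (5%) in osteosarcoma and 0 of 13 in what is evidently Ewing sarcoma, whose name is garbled there. These are small numbers on another drug. They support listing Cohort 3 by subtype, but they are not evidence about pooling across cohorts.

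**6. The safety text, side by side.** Section 5.4.1 has one dose level, so any table by dose group has one column. Time to first TEAE is the date of the first TEAE minus the date of the first dose, plus 1, but only for DLTs. As no DLT is defined, the analysis has no defined events.

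**The case against.** The best defence has four parts.

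- **The written objective is overall.** Section 2.1 asks about preliminary efficacy in advanced high-grade sarcoma and section 11.3.2 plans no test, so a descriptive overall ORR does answer it. This stands as far as it goes: the overall figure may be reported. It does not explain why the three cohorts that structure enrolment are absent from every efficacy analysis.
- **The wording may only name a denominator.** The protocol never says that cohorts are pooled, a SAP could add cohort tables, and undefined groupings (each group, treatment group) appear in the safety and disposition text. Part of this stands, since pooling is the plain reading and not an express statement. But the protocol itself fixes the primary estimator over all cases, and where section 11 does name a stratifier for its tables it names dose, so this is more than detail left to a SAP.
- **The size rests on assumed rates.** This is correct. The effect ranges from none to about 14 percentage points across the cases shown, according to how far the cohorts differ.
- **The dose-group wording is harmless.** Largely so: it collapses to one overall column and distorts no estimate. The DLT restriction is different, because it empties an analysis.

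A reader might also infer that, because the trial is open-label and section 11.2 leaves the final size open, cohorts will be closed on observed responses and their ORRs biased upwards. The document does not support this. It states no response-based rule, and slow accrual in a rare disease is an equally natural reading. Nor is the direction fixed. Suppose a true ORR of 20%, closure at 10 patients with fewer than 2 responders, and otherwise expansion to 30. The mean reported ORR is then 0.1 × 0.268 + (1.732 + 4 × 0.624)/30 = 16.8%, which is below the truth.

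**Conclusion.** The point holds in two limited parts and should be fixed.

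First, the primary ORR and the other efficacy measures are defined only over all cases, so the headline result depends on enrolment mix whenever the cohorts respond differently. The expected overall ORR spans 14.4-28.3% under one set of assumed rates, 13.3-17.3% under a milder set, and a single value if the rates are equal. The protocol cannot tell us which applies, because it gives no ASPS rate. It does not follow that the overall figure is meaningless or that the trial cannot be interpreted: cohort estimates can be computed from the same data.

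Second, the time-to-first-TEAE analysis and the DLT summary have no defined events, and the dose-group stratifier does not fit a trial with one dose level. The first of these loses an analysis; the second is an editorial fault.

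How each cohort's final size will be set deserves a sentence in section 11.2. That is a secondary clarification, not a demonstrated bias.

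**What to change.** - **Sections 2.4 and 11.3.7, and the synopsis:** make ORR with its exact 95% CI by cohort the primary analysis. Report DCR, PFS, DOR and OS by cohort as well. List Cohort 3 responses by subtype. Keep the overall figure and label it descriptive.
- **Sections 11.3.3 and 11.3.5:** replace the dose and dose-group splits with cohort and overall. Delete the DLT summary line and the DLT-only restriction, so that time to first TEAE covers all TEAEs.
- **Section 11.2 (secondary):** state how each cohort's final size between its minimum and maximum will be decided.

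**Cost.** Changed wording, more tables and wider intervals for the headline figures. At an observed 20%, the exact interval is 2.5-55.6% with 10 patients, 7.7-38.6% with 30 and 9.1-35.6% with 40, against 12.7-29.2% for 100 combined. That width is the real precision available for each cohort. No dose, visit or assessment changes.

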### **11.3.8 Biomarker Analysis**

To explore the expression of CD3, CD8, CD86, CD20, CD163, PD-L1, TGF- $\beta$ , CSF-1R and IL-1 $\beta$  in tumor tissues, and determine the presence of tertiary lymph node structure in tumor tissues based on the positive results in the above histological sections, so as to clarify the characteristics of the immunogenic microenvironment of TQB2858

in subjects with advanced high-grade sarcoma.

## 12. Original Document

In accordance with ICH E6, applicable regulations, and institutional requirements for the protection of subject personal information, each study site must maintain appropriate records related to the treatment and research related to this study. As part of a grant or participation in the study by CHIA TAI TIANQING Pharmaceutical Group, Nanjing Shunxin Pharmaceutical Co., Ltd., each site will permit the sponsor or its authorized representative and regulatory agency to inspect (or copy if legally permitted) the clinical records for quality review, audit, and evaluation of safety, study progress, and data validity.

The raw data are all information necessary for the reconstruction and evaluation of the clinical study and are original records of clinical findings, observations, or other activities. Examples of such source documents and data records include, but are not limited to, hospital records, laboratory notes, memoranda, subject diary cards, pharmacy dispensing records, recording of consultation meetings, recorded data from automated instruments, copies or transcriptions certified after verification as being accurate and complete, microfiches, photographic negatives, microfilm or disks, x-rays, and subject files and records kept at the participating pharmacy, at the laboratories, and at medico-technical departments.

Source documents were able to demonstrate the existence of the subject and substantiate the integrity of the data collected. Source documents are archived at the investigator's site.

Data transferred to the eCRF from source documents must be consistent with the source documents and any discrepancies must be explained. Depending on the trial, the investigator may need previous medical records or transfer records, or may need current medical records.

The investigator/institution will permit trial-related inspections, audits, IRB/IEC review, and regulatory inspection, providing direct access to all relevant source

data/documents. ECRFs/CRFs and all source documents, including disease records and copies of laboratory and medical test results must be available at all times for inspection by the sponsor's clinical research associates, auditors, and health authorities. The CRA and auditor may review all eCRFs/CRFs and written informed consents.

### **13. Quality Control and Quality Assurance**

In order to ensure the quality of the trial, the clinical study plan was discussed and formulated by the sponsor and the investigator before the formal start of the trial. Conduct GCP training for relevant study personnel participating in the trial.

Each study site must manage study drug according to the protocol and SOPs, including receipt, dispensing, recovery, storage, and destruction (if applicable).

According to GCP guidelines, necessary steps should be taken during the design and implementation stage of the study to ensure that the data collected are accurate, consistent, complete and credible. All the observed results and abnormal findings in the clinical trial shall be timely verified and recorded to ensure the reliability of data. The instruments, equipment, reagents and standards used for various inspection items in the clinical trial shall have strict quality standards and ensure that they work in the normal state.

The investigator entered the information required by the protocol into the eCRF, and the monitor verified whether it was completed completely and accurately, and instructed the site staff to make necessary corrections and additions.

The drug regulatory authorities, the Ethics Committee, the monitor and/or auditor of the sponsor may systematically inspect the activities and documents related to the clinical trial to evaluate whether it is conducted in accordance with the trial protocol, SOP and relevant regulations, and whether the trial data are recorded in a timely, true, accurate and complete manner. The audit does not directly involve the personnel conducting the clinical trial.

### **14. Ethics**

#### **14.1 Regulations/Declaration of Helsinki**

The investigator will ensure that the study is conducted in full compliance with the principles of "Declaration of Helsinki" or with the laws and regulations of the country in which the study is conducted, providing maximum protection to the subjects. The study must fully adhere to the principles of "Good Clinical Practice" in the ICH Tripartite Guideline (since January 1997) or local laws providing greater protection to the subjects.

#### **14.2 Informed Consent**

It is the responsibility of the investigator or designee of the investigator (if permitted by local regulations) to obtain written informed consent from each participating subject after adequate explanation of the aims, methods, anticipated benefits, and potential hazards of the study. For those subjects who are ineligible or unable to provide legal consent, written informed consent must be obtained from the legal guardian. If the subject and his/her legal guardian cannot read, an impartial witness must be present during the entire informed consent discussion. After the subject and guardian gave their verbal consent to participate in the study, the impartial witness signed the form to attest that the information on the informed consent was accurately explained and understood. The investigator or designee must also explain that the subject is free to refuse to participate or withdraw from the study at any time for any reason. If new safety information results in a significant change to the risk/benefit assessment, the informed consent form should be reviewed and updated as necessary. All subjects (including those already receiving treatment) should be informed of this new information and given a revised consent form to continue participation in the study.

